### Confidentiality {27}

All participants that enter the study will be kept anonymous. Identifiable information (name and signature) will only be located on the ICFs and household participation case report form, which will be stored securely on a locked electronic database, only accessible to delegated staff members. Participants will be assigned a unique ID number, which will be used on all other study documents and during analysis. The results of this study will be made available to the sponsors of this study and in publications, but no personal identifiers will be included.

### Plans for collection, laboratory evaluation and storage of biological specimens for genetic or molecular analysis in this trial/future use {33}

The blood samples will be tested in the Molecular Research Laboratory in Kampala in Uganda and destroyed after analysis is completed, following standardised protocols. Materials collected in this study will not be analysed outside Uganda, apart from air samples which will be analysed in laboratories at Loughborough University.

## Statistical methods

### Statistical methods for primary and secondary outcomes {20a}

#### Statistical analysis of the primary endpoint

The primary outcome will be reported as the proportion of children ≤ 5 years of age infected with malaria (%) at the cluster level. The proportion of children with malaria infection will be summarised at the cluster level and the intervention level. The outcomes will be compared across treatment arms. To address potential confounding factors and account for non-independence of data within clusters, logistic regression models will be employed. These models will incorporate a random effect for each study cluster to adjust for intra-cluster correlation.

Both unadjusted and adjusted models will be presented. The primary model will be as outlined above, and an adjusted model will include additional factors to account for variation at baseline and features that are highly predictive of the primary endpoint. These will include the following: Environmental factors known to have a strong influence on malaria incidence, including the average altitude, calculated from the mean spatial coordinate for each cluster, and the average distance from the nearest freshwater body, calculated from the mean spatial coordinate for each cluster; Use of other vector control interventions; Socio-economic status of the household; Architectural features of the household, or modification made to the household, that are related to mosquito entry; and Season of data collection.

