### Outcomes {12}

The primary outcome measured in this study will be the average reduction in malaria infection prevalence in children ≤ 5 years of age from baseline to month 12, as measured by RDT and microscopy. Secondary outcome measures include:
CDC light trap indoor density for anophelines and by anopheline species, as measured by light trap collections from 7 pm to 7 am on a 6 monthly basis. Change in mosquito density at baseline and month 12 between arms will be analysed by negative binomial regression with a random effect for study cluster.Anopheline-human contact (indoor and outdoor) using human biting rate (HBR) as an indicator for all anophelines and by anopheline species, as measured by HLC during 6-h intervals on a 6-monthly basis. Change in HBR at baseline and month 12 between arms will be analysed by negative binomial regression with a random effect for study cluster.Anopheline infectivity using sporozoite rate as an indicator for all anopheline and by anopheline species, as measured by laboratory detection of sporozoites in mosquito heads and thoraces from a subsample of anophelines collected during CDC light trap and HLC collections.Insecticide resistance, as measured by WHO tube test bioassay, during the intervention phase. Confirmed resistance, possible resistance and susceptibility will be calculated through evaluating knockdown and mortality rates.Subject behaviour and household features related to exposure to malaria and use of existing control tools, as measured by quantitative and qualitative surveys on a 6-monthly basis. Survey outputs will be summarised using basic statistics.Concentration of transfluthrin in air over the duration of an evening’s use or the Mossie-GO™ and the impact of indoor temperature on the concentration, as measured by air sampling at months 9 and 12. Mean concentration will be compared between arms.Acceptability of Mossie-GO™ in these communities, as measured be quantitative and qualitative surveys at 6 and 12 months and FGDs at 12 months. Outputs will be summarised using basic statistics and thematic analysis.Safety of intervention through monitoring of AEs and SAEs. Measured actively and passively throughout the duration of the study and total number of events and type of events will be compared between study arms.

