## Sample size {14}

Data collected from the study region suggest prevalence of malaria infection by RDT in children ≤ 5 years of age is 20%. A conservative coefficient of variation (CV) of 0.5 for between cluster prevalence was assumed. To detect a 40% reduction in prevalence with 90% power, we need 28 clusters per arm and a sample of 100 children in each cluster. Due to budget restrictions, sample size was reduced after baseline to 60 children in each cluster at 6 and 12 months, resulting in 86% power.

Entomological sample sizes were determined based on logistics, considering budget and personnel restrictions. The sample sizes of similar studies were also considered. For CDC light trapping, sampling will be carried out in all clusters and randomised at the household level. HLCs will be randomised at both the cluster and household level.

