## Assignment of interventions: allocation

### Sequence generation {16a}

All randomisation procedures will take place electronically. Treatment and control will be assigned as blinded, variables A and B, by the trial data manager and details of this assignment will be recorded in a sealed envelope and will not be shared with or accessible to any other team members.

The unit of randomisation is a cluster, corresponding approximately to villages within the study area. Clusters will be randomly assigned to two study arms, control and treatment intervention, using a computer-assisted constrained randomisation approach, facilitated by R [19]. To ensure adequate and feasible sampling, cluster selection will be restricted based on population size and population stability (Appendix Table 1). To reduce the impact of confounding factors, clusters will be stratified by land type (urban or rural) and study district, ensuring equal representation across both study arms. No significant inter-cluster variation was identified, meaning household selection within clusters will proceed as simple random sampling without blocking. This randomisation procedure involves generating 1000 unique sets of random treatment assignments. In each cycle, the differences in treatments allocated between district and land type strata will be assessed and the iteration with the least disparity, considered the most well-balanced iteration, will be selected as the final scheme for assigning treatments. Additional confounding factors will be factored into the statistical analysis (Appendix Table 2).

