#### Household survey

A questionnaire will be presented to the head of household at the point of malaria sampling to assess household characteristics and behaviours which may impact study outcomes. Questions within the survey will include, but not be limited to housing classification (urban, peri-urban, rural), housing characteristics (size, ventilation, construction materials), family structure (multiple families inhabiting one household, one family inhabiting multiple household structures etc.), number of children ≤ 5 years of age sleeping in the room with the Mossie-™unit, inhabitant(s) occupation(s), use of alternative vector control tools, whether occupants slept under a bed net the night before the survey, socio-economic status, number of inhabitants and their age and presence of domesticated animals (density and location). This survey will be conducted by the data collectors responsible for obtaining informed consent. All data will be inputted directly to forms on ODK.

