#### Statistical analysis of the secondary endpoints

For entomological outcomes, mosquito species composition will be reported as the total abundance and species-specific proportions of mosquitoes per sample per household per night. The outcomes will be compared across treatment arms. To address potential confounding factors and account for non-independence of data within clusters, logistic regression models will be employed, as described for the primary endpoint. Mosquito density will be reported as the total abundance of mosquitoes collected stratified by species. Additionally, for female *Anopheline* mosquitoes, the abundances will be broken down by blood fed/unfed, half gravid and fully gravid status. The outcomes will be compared across treatment arms. To address potential confounding factors and account for non-independence of data within clusters, a regression model will be employed with a negative-binomial log-link function to account for overdispersion typical of count data. These models will incorporate a random effect for each study cluster to adjust for intra-cluster correlation. Environmental covariates for factors, that were not controlled for with the allocation of clusters to trial arms, will be integrated into the models. These are average altitude and the distance from the nearest freshwater source per household, calculated from the mean spatial coordinate of each cluster. Comparative analyses will assess variations in mosquito species proportions across treatment arms to gauge effects of the intervention. Mosquito sporozoite rate will be reported as the proportion of mosquitoes (%) with sporozoites present per sample. The outcomes will be compared across treatment using the same linear regressions models employed for mosquito species composition. The prevalence of resistance to pyrethroids in *Anopheles* mosquitoes will be reported as the proportion of samples that are susceptible (98–100% resistance), possibly resistant (90–97% resistance) or confirmed resistant (less than 90% resistance) per sample. The outcomes will be compared across treatment arms. To address potential confounding factors and account for non-independence of data within clusters, logistic regression models will be employed, as described for the primary endpoint.

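### The primary outcome is a reduction from baseline, but the primary model names no baseline term, and neither listed model uses baseline cluster prevalence or the two allocation factors

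*Protocol article*

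**What the plan says.** Outcomes {12} of the protocol article states: "The primary outcome measured in this study will be the average reduction in malaria infection prevalence in children" aged 5 or under, from baseline to month 12, by RDT and microscopy.

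Statistical analysis of the primary endpoint describes something else. The proportion infected is summarised by cluster and by arm, and the arms are compared by logistic regression with a random effect for cluster. No baseline, visit or arm-by-time term is named. The section continues: "The primary model will be as outlined above, and an adjusted model will include additional factors to account for variation at baseline". The additional factors listed are altitude, distance to fresh water, other vector control, socio-economic status, house features related to mosquito entry, and season of data collection. Baseline prevalence, district and land type are not on the list.

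Sequence generation {16a} says "clusters will be stratified by land type (urban or rural) and study district", and Appendix Table 2 confirms that only these two factors were controlled in the allocation. Malaria prevalence monitoring fixes 100 children per cluster at baseline and 60 at months 6 and 12, with households redrawn at each survey.

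Sample size {14} gives the design assumptions: 20% prevalence; "A conservative coefficient of variation (CV) of 0.5 for between cluster prevalence was assumed"; and "To detect a 40% reduction in prevalence with 90% power, we need 28 clusters per arm" with 100 children each. It states 86% power after the cut to 60.

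**The concern.** Two things do not fit together.

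First, the outcome is worded as a change from baseline, while the model named as primary has no term through which baseline could enter. Someone implementing the plan could defend a follow-up-only comparison, a change score or a baseline-adjusted comparison. These target the same between-arm difference but have quite different power.

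Second, the adjusted model is introduced as dealing with variation at baseline, yet it leaves out the one direct measurement of that variation, 5,600 baseline tests across 56 clusters. It also leaves out the two factors that the allocation balanced. Sequence generation {16a} assigns only further confounders to the analysis. The usual practice is the reverse: a factor used to constrain the allocation belongs in the model, because otherwise the standard error takes no credit for the balance achieved.

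At stake is precision in a trial that has already reduced its follow-up sample for budget reasons, and an ambiguity in the primary analysis that should be closed before anyone sees data by arm.

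**Working it through.** **Inputs.** From Sample size {14}: control prevalence p0 = 0.20; 40% reduction, so p1 = 0.12; between-cluster CV k = 0.5; c = 28 clusters per arm; m = 100, later 60. Baseline m = 100. Assumed, because not stated: two-sided alpha 0.05, and a correlation rho between a cluster's true prevalence at baseline and at month 12, varied from 0 to 0.9.

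**Step 1: reproduce the plan's figures.** Variance of a cluster proportion: v(p, m) = p(1−p)/m + k²p².

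- m = 100: 0.0116 + 0.004656 = 0.016256. Clusters per arm = 1 + (1.96 + 1.2816)² × 0.016256 / 0.08² = 27.7, so 28. Power = Φ(√(27 × 0.0064 / 0.016256) − 1.96) = 90.3% (stated 90%).
- m = 60: 0.012667 + 0.00536 = 0.018027. Power = Φ(√(27 × 0.0064 / 0.018027) − 1.96) = 87.2% (stated 86%).

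Both figures describe one follow-up survey compared between arms, with no use of baseline.

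**Step 2: add baseline cluster prevalence.** Sampling error dilutes rho. The share of observed variance that is true between-cluster variance is 0.01/0.0116 = 0.862 at baseline. At follow-up it is (0.01/0.012667 + 0.0036/0.00536)/2 = 0.731. The squared observed correlation is therefore r² = rho² × 0.862 × 0.731 = 0.630 rho², and the follow-up variance is multiplied by 1 − r².

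**Step 3: raw change score.** Variance summed over the two arms:

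- control: 0.02(1 − rho) + 0.0016 + 0.002667
- intervention: 0.01 + 0.0036 − 0.012 rho + 0.0016 + 0.00176
- total: 0.041227 − 0.032 rho

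| rho | r² | Baseline-adjusted, formula | Follow-up only / adjusted, simulation | Change score, formula | Change score, simulation |
|---|---|---|---|---|---|
| 0 | 0 | 87.2% | 88.8% / 88.3% | 53% | 54% |
| 0.3 | 0.057 | 89.0% | 89.0% / 89.9% | 65% | 64% |
| 0.5 | 0.157 | 92.1% | 89.3% / 92.9% | 74% | 75% |
| 0.7 | 0.309 | 96.1% | 88.8% / 96.5% | 86% | 88% |
| 0.9 | 0.510 | 99.3% | 88.7% / 99.4% | 96% | 97% |

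The simulation used 6,000 trials per rho, 56 clusters and beta-distributed cluster prevalences, analysed as cluster proportions. All three analyses gave a mean between-arm difference of about −0.080, the true value. Under no effect at rho 0.7, follow-up only and baseline-adjusted analyses each rejected 5.2% of the time.

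By the formula, the change score reaches 86% at rho = 0.70 and equals follow-up only at rho = (0.041227 − 0.018027)/0.032 = 0.725. Baseline adjustment restores 90% power at rho of about 0.4 (r² = 0.101, power 90.4%).

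**Step 4: district and land type alone.** The between-cluster share of the follow-up variance is 0.0136/0.018027, about 0.75. If the two factors explained 5%, 10%, 20% or 30% of between-cluster variance (assumed), power at m = 60 would be about 88%, 90%, 92% or 94%.

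**The case against.** The best defence is that nothing is biased. Under randomisation, the month-12 contrast has the same expected between-arm risk difference as the difference in change, and the simulation confirms it. The stated 86% is the power of that comparison and is reproduced to within about a point. Leaving constrained factors out of the model tends to make the test conservative; it does not inflate type I error. All of this stands. A reader might infer that the primary model cannot estimate the intended effect or that the trial is underpowered against its plan. The documents support neither.

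A second defence is that the section does not say which surveys enter, and that listing season as a covariate hints at pooling, since baseline and month 12 both fall in June. An analysis plan exists and may settle this. That is fair on visit terms, and the power figures here assume a month-12 comparison. It does not cover the covariates, because the article itself names the primary model and lists what the adjusted one contains.

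Two further readings are tempting. One is that efficacy would be reported as one minus the odds ratio and so overstate the prevalence reduction. The protocol never defines it that way, and it also summarises proportions by arm. The other is that adjusting for net use or house features distorts the effect. The Household survey does ask "whether occupants slept under a bed net the night before the survey" at the point of malaria sampling, so month-12 values are measured after allocation. But this touches only the adjusted model, in a blinded trial whose placebo was chosen to limit behavioural differences, and the article does not fix which survey supplies these covariates. It is a query, not a demonstrated fault.

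**Conclusion.** The point holds as a mismatch between outcome and model, with forgone precision. It should be fixed, but it does not invalidate the analysis.

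The size rests on a correlation that the documents do not give. Taking formula and simulation together, baseline adjustment is worth about 0 points of power at rho 0, 2 at 0.3, 4–5 at 0.5, 7–9 at 0.7 and 11–12 at 0.9. The article's statement that stable environmental factors strongly influence malaria favours a positive correlation. Its remark under Sequence generation {16a} that no significant variation between clusters was found points the other way and sits uneasily with a CV of 0.5. At rho 0 the adjustment costs at most about half a point in the simulation, so there is little to lose.

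The real hazard is implementing the outcome wording literally. A raw change score would have roughly 53–75% power for rho up to 0.5, and would meet the stated 86% only at about 0.7 or above.

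**What to change.** Before database lock and unblinding, state the primary analysis as month-12 infection by arm, adjusted for baseline cluster prevalence, district and land type, with a random effect for cluster. Reword Outcomes {12} so that it describes this baseline-adjusted comparison at month 12, and say explicitly that a raw change score will not be used. Keep the model without covariates as a sensitivity analysis.

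The cost is three model terms, about three degrees of freedom out of 56 clusters, and a wording change in the protocol and analysis plan. The data are already collected or scheduled.

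As a secondary suggestion, the adjusted model could take net use and house features from the baseline household survey as cluster summaries, so that every covariate precedes device distribution.

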### Relevant concomitant care permitted or prohibited during the trial {11d}

The study design will not withhold standard-of-care for clinical management of malaria or vector control interventions (ITNs, IRS or larviciding) in either control or intervention arms; however, use of other interventions will be monitored and recorded throughout the study period. Study participants will also be encouraged to adhere to standard vector control interventions (such as use of ITNs). This will allow for evaluation of the impact of the spatial repellent device assuming all other measures are still occurring for malaria prevention, providing insight into the additive benefit above that provided by currently recommended WHO malaria preventative measures and further exploring the impact of using multiple interventions.

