#### Malaria prevalence monitoring

One hundred children per cluster at baseline and sixty children per cluster at months 6 and 12, selected at random from separate households, will be sampled for malaria infection. A master list of households will be generated listing households with children ≤ 5 years of age and households will be randomly selected with replacement at each of the time points. If there are multiple children ≤ 5 years of age within the household, the Kish Grid method will be used to select the participant [22]. The study will be explained and consent obtained from the child’s parent/guardian before enrolling the child in the study. Once enrolled, the age and sex of the participant, along with use of other vector control products and antimalarial drugs will be recorded. A fingerstick blood sample will be taken for malaria RDT, a blood smear for analysis by microscopy and a blood spot for analysis by PCR at a later date. All participants will be eligible for malaria treatment, if they test positive by RDT at any sampling time point. This will be accessed following national standard of care guidance at their local health care facility or through the VHTs. Trained laboratory technicians will be responsible for blood sampling, reading and recording results and sample analysis via microscopy and PCR. Microscopic examination of slides will be conducted two times, independently in verified reference laboratories. Participant data and results will be collected manually on paper logs and then entered into Open Data Kit (ODK) software [23].

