### Methods for additional analyses (e.g. subgroup analyses) {20b}

There is no formal statistical analysis planned for subgroups for this study.

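### The supportive adjusted model for the primary endpoint is open to using net use and house modifications recorded after devices are in use, so its estimate may be neither a baseline adjustment nor the total effect

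*Protocol article*

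**What the plan says.** All references are to the protocol article.

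- **Statistical analysis of the primary endpoint.** The primary model is a logistic regression with a random effect for cluster. A separate adjusted model adds factors for two stated purposes: differences present at baseline, and strong predictors of infection. Both models will be reported. The added factors include "Use of other vector control interventions; Socio-economic status of the household; Architectural features of the household, or modification made to the household", together with altitude, distance to water and season. The section does not say which survey round supplies the values.
- **Household survey.** "A questionnaire will be presented to the head of household at the point of malaria sampling". The items include other vector control tools and whether occupants used a net the previous night.
- **Malaria prevalence monitoring.** "households will be randomly selected with replacement at each of the time points". The child's use of other vector control products is recorded when the child is enrolled for sampling.
- **Implementation {16c}.** Devices are handed out directly after baseline data collection.
- **Outcomes {12}.** Behaviour and household features, including use of existing control tools, form a secondary outcome measured every six months.

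**The concern.** For a child tested at month 6 or 12, the household value that comes with the blood sample was recorded after devices had been in the home for months. Net use and changes to the house are things a working device could alter. The Intervention description {11a} expects treated discs to prevent bites and kill some mosquitoes, and a household that notices this may rely less on nets. The placebo device equalises ownership of a device, but not the experience of one that works.

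A covariate measured after randomisation cannot confound a randomised comparison, but it can be a consequence of treatment. Adjusting for it removes whatever part of the effect runs through it. The result would then be neither the baseline adjustment that the section describes nor the total effect of handing out the device. At stake is how the adjusted estimate is read beside the primary one, particularly if the two disagree.

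**Working it through.** **1. The plan's own figure.** Sample size {14} gives "To detect a 40% reduction in prevalence with 90% power, we need 28 clusters per arm and a sample of 100 children in each cluster", with control prevalence 20% and "A conservative coefficient of variation (CV) of 0.5 for between cluster prevalence was assumed". I used the Hayes–Moulton formula for unmatched clusters, with a two-sided 5% level (my assumption), p0 = 0.20, p1 = 0.12 and k = 0.5:

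c = 1 + (1.960 + 1.282)² × V / (p0 − p1)², where V = p0(1 − p0)/m + p1(1 − p1)/m + k²(p0² + p1²).

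- m = 100: V = 0.0016 + 0.001056 + 0.0136 = 0.016256, so c = 27.69, rounded up to 28. This reproduces.
- m = 60, 28 clusters: V = 0.018027. Power = Φ(√(27 × 0.0064 / 0.018027) − 1.960) = 87.2%, against the stated 86%. This is close enough.

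The present point changes neither figure. Only the 20% prevalence is carried forward.

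**2. Could baseline values be attached to each follow-up household?** Not to all. With 100 of N eligible households surveyed at baseline and an independent redraw later, the expected share without a baseline survey is 1 − 100/N. The documents bound N loosely. Appendix Table 1 requires more than 109 eligible households (N = 110 gives 9%), Recruitment {15} says more than 150 (N = 150 gives 33%), and Appendix Table 1 caps total households at 245 (59% if all were eligible). A household-level baseline covariate would therefore be missing for roughly 9 to 59% of follow-up households. A baseline cluster mean is available for every cluster.

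**3. Total against net-adjusted effect.** Assumptions not in the documents: the net-use levels, net-use odds ratio r = 0.4 to 0.6, and device odds ratio d at fixed net use.

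- Solve for the intercept a so that control prevalence is 20% at 70% net use: 0.7·expit(a + ln r) + 0.3·expit(a) = 0.20.
  - r = 0.4: a = −0.798 (prevalence 0.311 without a net, 0.153 with).
  - r = 0.6: a = −1.045 (0.260 and 0.174).
- Apply d = 0.55 in the active arm.
  - r = 0.4: 0.1985 without a net, 0.0901 with.
  - r = 0.6: 0.1621 and 0.1040.
- Active-arm prevalence at net use u is P(u) = u·p(net) + (1 − u)·p(no net). The total reduction is 1 − P(u)/0.20. The net-adjusted reduction holds u at 0.70.

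| Device OR | Net use, control vs active | Total reduction (r = 0.4; r = 0.6) | Net-adjusted reduction (r = 0.4; r = 0.6) |
|---|---|---|---|
| 0.55 | 70% vs 70% | 38.7%; 39.3% | 38.7%; 39.3% |
| 0.55 | 70% vs 60% | 33.3%; 36.4% | 38.7%; 39.3% |
| 0.55 | 70% vs 50% | 27.8%; 33.5% | 38.7%; 39.3% |
| 0.55 | 70% vs 80% | 44.1%; 42.2% | 38.7%; 39.3% |
| 0.80 | 70% vs 50% | 2.3%; 9.0% | 16.2%; 16.5% |

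Example, r = 0.4 and u = 0.6: P = 0.6 × 0.0901 + 0.4 × 0.1985 = 0.1335, so the reduction is 1 − 0.1335/0.20 = 33.3%.

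**4. Simulation at trial size.** Settings: 28 clusters per arm, 60 children each, 150 replicates, logistic GEE, device odds ratio 0.75, net-use odds ratio 0.5, control net use 80%.

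| Active-arm net use | Unadjusted OR | Adjusted OR |
|---|---|---|
| 80% | 0.74 | 0.74 |
| 60% | 0.90 | 0.77 |
| 90% | 0.68 | 0.74 |

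At 60%, a significant benefit appeared in 14% of unadjusted runs and 43% of adjusted runs.

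Only net use is quantified here. House modification would act by the same mechanism.

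**The case against.** Several objections stand, and they limit the point.

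- **The primary result.** A reader might infer that the trial's main estimate is biased. It is not. The model without these covariates is primary and both are presented, so any loss of net use stays in the primary estimate and a gap between the models would be visible.
- **Concealment.** A reader might infer that a switch from nets to the device would go unreported. Use of existing tools is a secondary outcome and survey data will be summarised. Only a comparison by arm is not spelled out.
- **Direction.** A reader might infer that adjustment flatters the device. That requires lower net use in the active arm. Higher use there reverses the bias and equal use removes it. Blinding, the placebo device and encouragement of standard measures in both arms make a difference less likely, and no figure in the documents supports a particular gap.
- **Timing.** It is inferred. Baseline cluster summaries are not excluded, and the list also serves to capture strong predictors.
- **Stated aim.** The concomitant care section {11d} speaks of "providing insight into the additive benefit above that provided by currently recommended WHO malaria preventative measures and further exploring the impact of using multiple interventions", on the assumption that other measures continue. An estimate at fixed net use could be a legitimate secondary quantity, although it would not be a baseline adjustment or the total effect.
- **Subgroups.** Section {20b} says "There is no formal statistical analysis planned for subgroups for this study". A reader might see a conflict with {11d}, but only formal subgroup analysis is excluded, and an exploratory look at combined use remains open. An interaction test would be a preference, not a correction.

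What the objections do not remove is the double role of control-tool use as both outcome and covariate, with nothing to confine the covariate to pre-device values.

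**Conclusion.** The point holds for the supportive adjusted model only. As listed, its vector-control and house-modification terms would normally take values recorded after device distribution, and adjusting for them can move the estimate away from the total effect.

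The size depends on assumptions outside the documents. With a device odds ratio of 0.55 and net-use odds ratios of 0.4 to 0.6, a 10-point gap in net use opens a difference of about 3 to 5 percentage points between total and adjusted reduction, in the direction set by which arm uses nets less. With a weaker device (odds ratio 0.8) and a 20-point loss in the active arm, the total is 2 to 9% against 16 to 17% adjusted. With no difference between arms there is no bias. The primary analysis, the sample size and the power are untouched. This is worth correcting because the correction is cheap, not because the main conclusion is in danger.

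**What to change.** In the section on statistical analysis of the primary endpoint:

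1. State that the covariates for other vector control and for house features or modifications are pre-distribution values, entered as cluster means from the baseline household survey (100 households per cluster).
2. Report net use and other vector-control use by arm at months 6 and 12, as part of the existing secondary outcome.
3. Label any model that uses follow-up values of these variables as exploratory, and say that it does not estimate the total effect.

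The cost is wording, since the data are already collected or planned. The one statistical downside is that cluster-level baseline means explain less variation between individual children than household-level follow-up values would.
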